#### **Monitoring and reporting of Adverse Events**

Safety will be evaluated in the mother, the foetus and the newborn. Active safety monitoring will consist in daily phone visits to study participants from the initiation of treatment administration to assess drug tolerability and record all Adverse Events (AEs). In addition, a health facility-based passive surveillance system will be established to capture unscheduled visits of participants during follow-up.

The Principal Investigators (PI) at each study site will be responsible for recording, managing, and reporting of the AEs and SAEs as per study protocol. All AEs will be recorded in the AE form, and the DSMB will agree which SAEs and in what time frame will be reported.

All SAEs will be recorded on the SAE form and will be reported within 24 or 48 hours to the sponsor's (ISGlobal) Safety Coordinator, the CRO Dynamic Solutions, and to the DSMB as per study protocol. A flowchart will be provided to each study site to train the procedures for assessing AEs and reporting requirement according to severity and expectedness as well as persons responsible for recording and reporting of AEs/SAEs.

All participants enrolled in the trial will be educated at the beginning of the study on how to and whom to contact if they experience any untoward event and/or get admitted to the hospital.

In addition, Interim Safety Reports and Annual Safety Reports will be prepared by the Safety Coordinator and the CRO Dynamic Solutions and distributed to the local Ethic Committee, Sponsor, and DSMB as agreed in the study protocol.

The CRO Dynamic Solutions will ensure that AEs and SAEs are reported in compliance with International Conference on Harmonisation (ICH) Good Clinical Practice (GCP) guidelines and current international legislation during COVID-19 pandemic.

#### **f. Data management**

Data will be directly collected and entered in the electronic database through mobile devices. Therefore, electronic Case Report Form (eCRFs) will be developed for capturing of the trial's data. As the CRO Dynamic Solutions will be in charge of the management of the trial's data, their proposed Clinical Data Management System (CDMS) will be used. In this case, e-Clinical will be used. e-Clinical is a web-based CDMS developed by Dynamic and following all safety law requirements described in the clinical investigation projects normative 21 CRF Part II.

Data will be then directly entered in the study database in electronic format following trial's Standard Operating Procedures (SOPs) in which study nurses will be trained. A Data Validation Plan (DVP) specifying all the Data Quality Checks (Data Queries) will be developed by the CRO to assure and control the quality of the data. These checks will be then programed into the eCRFs. Thus, data quality will be addressed at different levels. At the low level, data will be validated during data entry, i.e. when the study nurses are completing the eCRFs. Any error will be warned to the nurses then to be solved, if possible, during the completion of the eCRF. The intermediate level will be triggered once the data is sent to the server through the web application. At that point, a qualified data manager will verify that all the Data Quality Checks defined in the DVP

are met. At the highest level, during the proposed routine monitoring visits defined in the Monitoring Plan, the quality of a subset of the records produced during the study will be assessed and validated.

A Data Management Plan (DMP) and the Monitoring Plan will be prepared by the CRO describing in detail all the aspects related to the data management and monitoring of data.

Concomitant medications registered on the database will be coded using the WHO Drug Reference List, which employs the Anatomical Therapeutic Chemical classification system. Medical history/current medical conditions and adverse events will be coded using the Medical dictionary for regulatory activities (MedDRA) terminology.

#### **g. Quality assurance and quality control**

Implementation of this study will be directed by the protocol as well as study specific SOPs. Quality assurance and quality control systems will be implemented and maintained with eSOPs to ensure that trials are conducted and data are generated, recorded and reported in compliance with the protocol, GCP, and the applicable regulatory requirement(s).

The eSOPs will outline procedures for conducting study visits, data and forms processing, AE assessment, management and reporting, dispensing study drugs and documenting drug accountability, and other study operations.

Close cooperation between the sponsor, investigators, biostatisticians, data managers, and other study team members will be necessary in order to track study progress, respond to queries about proper study implementation, and address other issues in a timely manner. Assignment of all sponsor and investigator responsibilities for this project are specified in the project Consortium Agreement.

#### **h. Trial monitoring**

The objectives of the trial monitoring are the following:

- To ensure that for all trial's records reviewed, the participants meet eligibility criteria, including a signed informed consent document
- To ensure that data entered into the electronic case report forms (eCRFs) are accurate and complete for all fields that will be reviewed
- To ensure that the on-site source documentation is consistent with the data entered into the eCRFs
- To ensure that regulatory documentation is present, complete and in compliance with GCPs, ICH and local regulations.
- To ensure that all study drugs are handled in accordance with investigational product procedures and accountability is accurately documented
- To ensure that the study is being conducted in compliance with the protocol, the SOPs, the GCP and local regulations.
- To ensure that site has written laboratory procedures, documentation of instrument calibration, and QA policies. A specimen audit will also be performed
- To ensure that site's trial and regulatory documents are in place, updated, and stored appropriately

The clinical monitoring will be performed by the CRO Dynamic Solutions. They will prepare the Monitoring Plan and will define the different types of monitoring visits.

### **i. Data analysis**

The data analysis plan will be developed by the CRO Dynamic Solutions in collaboration with all investigators. In general, it will include the following aspects:

#### **Statistical analysis populations**

The assignment of participants into analysis populations will be performed prior to database lock and any data analysis. The following populations are defined:

a) Intention to treat (ITT)

This population will include all randomized pregnant women and will be the target population for the efficacy analysis. Following the intention-to-treat principle, patients will be analyzed according to the treatment they were assigned to at randomization.

b) According to protocol (ATP)

This population will include all women who fulfil all the inclusion-exclusion criteria, took the 14 days HCQ treatment and from whom data is available for the analysis.

c) Safety

This population will include all patients who received at least one dose of HCQ/placebo and had at least a follow-up visit. The participant's safety will be analyzed by trial arm.

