#### **b) Treatment arm allocation**

Participants will be then randomized in a 1:1 ratio to HCQ (400 mg/day for three days, followed by 200 mg/day for 11 days) or placebo (2 tablets for three days, followed by one tablet for 11 days).

Allocation of participants to study arms will be done centrally by the trial's Sponsor (the Barcelona Institute for Global Health, ISGlobal) by block randomization. This method will ensure balanced allocation to both arms. The electronic CRF will assign automatically a study number to each participant, depending on her study group and recruitment site. Each number will be related to a treatment number, which assigns them to one of the study arms. Randomizations lists with treatment assignment for each study participant will be concealed in opaque sealed envelopes and only open in case of urgent need following study unblinding procedures.

A study card will be given to the participant in order to facilitate their clinical management in case they attend primary care centres or other hospitals.

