#### **Statistical models and methods of analysis**

The primary analysis of the trial will be:

- The comparison of the proportion of negative SARS-CoV-2 PCR at day 14 after initiating treatment administration among those women who were SARS-CoV-2 PCR positive at recruitment in the ITT and ATP cohorts.
- The comparison of the proportion of pregnant women who were negative SARS-CoV-2 PCR at recruitment and close contacts of confirmed cases of SARS-CoV-2 infection, with a positive PCR for the infection at day 14, in the ITT and ATP cohorts.

Proportions will be compared between the two intervention-arms within each group using the Fisher exact test and presented as relative risk ratio (RR) or reduction of the RR ( $1 - RR * 100\%$ ) if RR lower than 1. Adjustment for co-variables and possible confounders will be done using Poisson regression with a log link and robust estimate of the covariance (Huber method), using the method proposed by Zou et al. 2014 and 2013.

Continuous variables will be compared between groups using Wilcoxon rank sum test and the effect presented as Mean Difference. Adjustment for co-variables and possible cofounders will be done using ordinary least square regression. Variables will be transformed to the logarithm scale if normality is improved and results presented as Proportional Difference. If after transformation, non-normality of the residuals is detected using diagnostic regression plots, robust intervals of confidence and Wald test will be presented instead.

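### The according-to-protocol set is worded around HCQ alone and stands unranked beside ITT in the primary analysis, and the safety set drops dosed women who have no follow-up visit

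*Protocol*

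**What the plan says.** Protocol section 5.i, Statistical analysis populations, defines three sets.

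- **ITT:** "This population will include all randomized pregnant women and will be the target population for the efficacy analysis".
- **ATP:** women who meet all eligibility criteria, "took the 14 days HCQ treatment and from whom data is available for the analysis". Placebo is not mentioned.
- **Safety:** women who "received at least one dose of HCQ/placebo and had at least a follow-up visit". Here both products are named.

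In the same section, Statistical models and methods of analysis introduces two comparisons as the primary analysis of the trial. One concerns women who were PCR positive at recruitment, the other PCR-negative contacts. Each is to be made "in the ITT and ATP cohorts". The test is between arms: "Proportions will be compared between the two intervention-arms within each group using the Fisher exact test". Nothing there ranks the two cohorts or says what happens if they disagree.

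**The concern.** Three rules in this section do not work as written.

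1. **ATP wording.** Membership depends on having taken HCQ, yet the set is to be used for a comparison of HCQ with placebo. The wording also cannot be applied blind. Populations are to be assigned before database lock, and section 5.c (Administration of study drugs) keeps all personnel blinded throughout.
2. **Two cohorts in the primary analysis.** With the wording repaired, ITT and ATP still stand together as primary. ATP membership depends on completing 14 days of tablets, which is decided after randomisation and may be related to tolerability. If the cohorts disagree, the text could support a claim from either one.
3. **Safety set.** A woman who takes the supervised first dose, has an event and leaves before any follow-up visit is outside the set, even if passive surveillance recorded the event.

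At stake are a clear basis for the efficacy claim and a complete account of harm in pregnant women.

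**Working it through.** **Inputs.** Allocation is 1:1 (section 5.c, Treatment arm allocation). The Sample size section of 5.a gives 257 contacts per arm and 100 women in each infected group, so 50 symptomatic plus 50 asymptomatic = 100 infected per arm. It assumes 3% infection in control contacts and a 3-point reduction (0% on HCQ), with 80% power and two-sided 0.05.

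**The plan's own figure.** Pooled normal approximation, no continuity correction, mean proportion (0.03 + 0)/2 = 0.015:

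n = [1.960 × √(2 × 0.015 × 0.985) + 0.842 × √(0.03 × 0.97)]² / 0.03² = 256.5, rounded up to 257 per arm.

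This reproduces the protocol's number. It is used below only for arm sizes.

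**ATP membership.**

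| Group | Literal wording: HCQ vs placebo (maximum) | Assigned study medication: HCQ vs placebo (maximum) |
|---|---|---|
| Contacts | 257 vs 0 | 257 vs 257 |
| Infected (50 + 50 per arm) | 100 vs 0 | 100 vs 100 |

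With an empty placebo column, neither a Fisher test nor a relative risk can be computed. The planned total of 714 is the same under either wording.

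**How easily ITT and ATP could disagree among contacts.** Expected control infections are 257 × 0.03 = 7.7, about 8. The counts below are assumed for illustration; p-values are two-sided Fisher exact.

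| Cohort | HCQ infections | Placebo infections | p |
|---|---|---|---|
| ITT | 2 of 257 | 8 of 257 | 0.106 |
| ATP, one infected HCQ woman removed | 1 of 256 | 8 of 257 | 0.037 |
| ATP, HCQ arm reduced to 240 | 1 of 240 | 8 of 257 | 0.038 |

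One infected HCQ woman who did not complete 14 days is enough to move the result across 0.05. Shrinking the HCQ arm further barely matters; what matters is the loss of the single event.

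**Safety set.** The number excluded depends on what counts as a follow-up visit, and the protocol points both ways.

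- Section 5.e (Monitoring and reporting of Adverse Events) speaks of daily phone visits from the start of treatment, and Table 1 has a column for follow-up visits during the intervention. If these count, a woman is lost only when there is no contact at all after dosing.
- The summary table at the front uses the term follow-up visit for day 21, and the section 5.c text on household and follow-up visits describes only day 21. If that is the meaning, any dosed woman who withdraws or dies before day 21 is lost.

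The protocol gives no dropout or discontinuation rate, so the number cannot be computed under either reading.

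**The case against.** A reader might infer that the placebo arm would really vanish from the ATP analysis. The document does not support that. The analysis text compares two arms in the ATP cohort, the safety definition a few lines later names both products, and section 5.c speaks of study medication. The intended meaning is clear, and this objection stands: the ATP wording is a drafting error with an obvious correction.

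It can also be argued that calling ITT the group that "will be the target population for the efficacy analysis" already supplies the ranking, that ATP is merely reported alongside, and that the separate data analysis plan may settle the matter. This is a fair reading and it softens the conflict. It does not remove it, because the protocol itself lists both cohorts under the primary analysis. The two populations also overlap heavily. No inflation of the type I error has been calculated here, and none should be claimed; the point is the missing decision rule. Selection after randomisation is a feature of any per-protocol set and is no error while that set is supportive.

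On safety, a reader might infer that early toxicity withdrawals are removed and harm on HCQ is understated by some definite amount. The document does not support this. Stopping the drug is not leaving follow-up: section 5.e has each adverse event followed until it resolves or is judged permanent, and serious events go to the Safety Coordinator and the DSMB whatever the analysis set. If the phone visits count, the loss is probably small. What stands is that the condition is undefined and serves no stated purpose.

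**Conclusion.** The point holds as a set of corrections to stated rules.

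- The ATP definition is wrong as worded, almost certainly through a slip, and cannot be applied blind. The ITT comparison is untouched.
- The primary analysis names two populations without a rule for disagreement. With about 8 expected control infections among contacts, one woman can change the conclusion (p = 0.106 against p = 0.037). This rests on the protocol's 3% control rate and on assumed counts of 2 and 8 infections; it shows that disagreement is possible, not how likely it is.
- The safety set excludes some dosed women. The number is small if daily phone visits count and larger if only day 21 counts. No percentage can be attached to it from this document.

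The corrections are worth making before analysis because they are nearly free. Nothing here shows that the trial's ITT result would be biased.

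**What to change.** Make three wording changes in section 5.i.

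1. **ATP definition:** replace the HCQ condition with: took the assigned study medication (HCQ or placebo) for 14 days.
2. **Statistical models and methods of analysis:** state that ITT is the sole primary population for both primary comparisons, and that ATP is supportive and cannot replace the ITT conclusion.
3. **Safety definition:** all women who received at least one dose of HCQ or placebo, with the follow-up-visit condition deleted. Events at the supervised dose or found through passive surveillance then count.

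The cost is a short amendment, carried into the data analysis plan. Sample size, visits and clinical management do not change.

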#### **Patient demographic data and other baseline characteristics**

All data will be listed and will consist of data collected/measured prior to randomization. Background and demographic characteristics of patients will be summarized for study arm.

Variables included in this analysis will be: maternal age, gestational age at recruitment (mean and by category), parity (mean and by category), ethnic group, municipality, previous ANC visits before the recruitment, height (cm) and Hb results at first ANC visit.

#### **Statistical models and methods of analysis**

The primary analysis of the trial will be:

- The comparison of the proportion of negative SARS-CoV-2 PCR at day 14 after initiating treatment administration among those women who were SARS-CoV-2 PCR positive at recruitment in the ITT and ATP cohorts.
- The comparison of the proportion of pregnant women who were negative SARS-CoV-2 PCR at recruitment and close contacts of confirmed cases of SARS-CoV-2 infection, with a positive PCR for the infection at day 14, in the ITT and ATP cohorts.

Proportions will be compared between the two intervention-arms within each group using the Fisher exact test and presented as relative risk ratio (RR) or reduction of the RR ( $1 - RR * 100\%$ ) if RR lower than 1. Adjustment for co-variables and possible confounders will be done using Poisson regression with a log link and robust estimate of the covariance (Huber method), using the method proposed by Zou et al. 2014 and 2013.

Continuous variables will be compared between groups using Wilcoxon rank sum test and the effect presented as Mean Difference. Adjustment for co-variables and possible cofounders will be done using ordinary least square regression. Variables will be transformed to the logarithm scale if normality is improved and results presented as Proportional Difference. If after transformation, non-normality of the residuals is detected using diagnostic regression plots, robust intervals of confidence and Wald test will be presented instead.

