## Synopsis

The emergence of severe acute respiratory syndrome coronavirus 2 (SARS-CoV-2) disease (COVID-19) in China at the end of 2019 has caused a large global outbreak and is a major world public health issue. Since the onset of the SARS-CoV-2 epidemic, very few studies have reported on the effects of the infection on maternal health. Importantly, pregnant women should be considered a population at increased risk of infection, given the greater risk of severe morbidity and mortality from SARS and influenza. Pregnancy is considered a period of susceptibility for infections, including respiratory pathogens and severe pneumonia. Regarding SARS-CoV-2 it is still unclear how the infection affects pregnant women and their offspring, as well as which factors may influence maternal disease and outcomes.

This is a randomized, double blinded, placebo-controlled multicentre clinical trial including 714 pregnant women (200 SARS-CoV-2 infected -100 symptomatic with mild disease and 100 asymptomatic- pregnant women and 514 SARS-CoV-2 uninfected pregnant women who are contacts with a SARS-CoV-2 case) with the main objectives of assessing the safety and efficacy of oral hydroxychloroquine (HCQ) in reducing maternal viral shedding by PCR, and preventing incident SARS-CoV-2 infection and disease severity. Pregnant women undergoing antenatal follow up at five maternity hospitals, presenting at least one sign and/or one mild suggestive symptoms and a positive SARS-CoV-2 PCR test, or who are contacts of a suspected or confirmed case, will be recruited and randomised 1:1 to receive HCQ orally (400 mg/day for 3 days, followed by 200 mg/day for 11 days) or placebo. Women will be followed up for the duration of the intervention. One week after intervention completion, a SARS-CoV-2 PCR test will be repeated. At delivery, the pregnancy outcome will be registered and a cord blood sample will be collected to measure for IgG and IgM of SARS-CoV-2. A neonatal nasopharyngeal aspirate will be collected to perform PCR SARS-CoV-2 testing.

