#### Primary endpoint

Number of PCR-confirmed infected pregnant women assessed from collected nasopharyngeal and oropharyngeal swabs at day 21 after treatment start (one week after treatment is completed).

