#### **Sample size**

A sample size of 100 infected pregnant women of each asymptomatic and symptomatic group, 1:1 randomly allocated into two study arms, allows to detect an effect size of 30%, 34% and 39% with 80% power and two-tail type-I error of 0.05 assuming 3%, 10% and 30% curation rates in the control group, respectively. In other words, this sample allows detecting differences if the cure rates in the intervention group are at least 33%, 44%, and 69%, respectively. A sample size of 257 non-infected, contact positive, pregnant women per intervention arm will be needed to detect a 3 % reduction in the prevalence of infection with 80% power and two-tail type-I error of 0.05, assuming a prevalence of infection in the control group of 3% after two weeks of follow up.

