#### **Household and follow-up visits**

At day 21 after initiating study drugs' administration (one week after treatment completion), study personnel will visit women at home or at the hospital to collect a nasopharyngeal and oropharyngeal swabs for PCR -SARS-CoV-2 and to perform an ECG.

The study personnel will assess treatment adherence by requesting and counting if there are remaining study pills.

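### Both primary comparisons are set at day 14, but the primary endpoint and the only scheduled PCR swab after baseline are at day 21

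*Protocol*

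**What the plan says.** The protocol gives the time of its primary PCR outcome in several places.

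- **Statistical models and methods of analysis (5.i).** For women PCR-positive at recruitment: "The comparison of the proportion of negative SARS-CoV-2 PCR at day 14 after initiating treatment administration". For PCR-negative contacts, the outcome is the proportion "with a positive PCR for the infection at day 14, in the ITT and ATP cohorts".
- **Primary endpoint (5.a).** PCR-confirmed infection is read from swabs taken "at day 21 after treatment start (one week after treatment is completed").
- **Household and follow-up visits (5.c).** "At day 21 after initiating study drugs' administration (one week after treatment completion), study personnel will visit women at home or at the hospital" to take the swabs.
- **Synopsis.** "One week after intervention completion, a SARS-CoV-2 PCR test will be repeated".
- **Table 1.** The maternal swab is marked at enrolment and at the household visit one week after treatment ends. The cell for follow-up during the intervention is empty.
- **Sample size (5.a).** The contact group is sized "assuming a prevalence of infection in the control group of 3% after two weeks of follow up".

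**The concern.** The analysis section and the endpoint section name different days for the same primary outcome, and the visit schedule supplies data for only one of them. Day 14 is the last day of treatment and day 21 is a week off treatment. Viral clearance and new infection can both change in that week, so these are two different outcomes and not two labels for one.

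Read literally, the primary analysis has no planned data. An analyst would have to depart from the stated analysis or fall back on whatever swabs happened to be taken near day 14. In either case the main result would rest on a decision that the protocol did not make. The contact sample size also rests on a two-week infection rate, while the endpoint is read at three weeks.

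**Working it through.** **1. Fix the calendar.** Treatment is three days at the first dose level plus 11 days at the second: 3 + 11 = 14 days. One week later is 14 + 7 = day 21. The Primary endpoint section, the visit text, the Synopsis, Table 1 and the summary table at the front of the protocol (which gives the day-21 follow-up visit but does not mention a swab) therefore agree with each other.

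**2. Test whether day 14 could mean the day-21 visit.** It cannot. The first comparison counts its 14 days from the start of treatment. Counting from the end of treatment would give 14 + 14 = day 28, and no swab is scheduled then either.

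**3. Count the scheduled maternal PCR samples after baseline.**

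| Source | Day 14 | Day 21 |
|---|---|---|
| Primary endpoint | no | yes |
| Household and follow-up visits | no | yes |
| Synopsis | no | yes |
| Table 1 | no | yes |
| Primary analysis, infected women | yes | no |
| Primary analysis, contacts | yes | no |

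During the 14 treatment days the scheduled contact is a daily phone call, with no sampling. Scheduled day-14 PCRs: 0 of 714 planned women. Scheduled day-21 PCRs: 714 of 714.

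**4. Check whether unscheduled swabs could supply day 14.** A footnote to Table 1 allows a PCR at any time when a woman has fever and/or two suggestive symptoms. Such swabs are selected by symptoms, which are related to the outcome, and they are not tied to day 14. The intention-to-treat population is all randomised women, so these swabs cannot provide its outcome. The according-to-protocol population requires available data, so a day-14 analysis would reduce it to women who happened to be swabbed then.

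**5. Reproduce the contact sample size.** Inputs from the Sample size section: control p1 = 0.03, intervention p2 = 0 (a 3-point reduction from 3%), two-sided alpha 0.05, power 80%, 1:1 allocation. With pooled variance under the null and no continuity correction:

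n = [1.960 × √(2 × 0.015 × 0.985) + 0.8416 × √(0.03 × 0.97 + 0)]² / 0.03²

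= [1.960 × 0.1719 + 0.8416 × 0.1706]² / 0.0009

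= 0.4805² / 0.0009 ≈ 256.5, rounded up to **257 per arm**, or 514 in total.

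This is the protocol's figure (power at 257 per arm: 80.1%). So the 3% rate drives the contact sample size, and that rate is stated for two weeks.

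**6. Carry the rate to day 21.** The protocol gives no day-21 rate. New infections in the third week would raise PCR positivity at day 21. Clearance of infections acquired early would lower it. Neither the direction nor the size of the change follows from the documents, so no day-21 sample size is offered here.

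**The case against.** The strongest reply is that the endpoint is already fixed. The Primary endpoint section names day 21 and every scheduling passage fits it. The Data analysis section describes itself as general and defers to an analysis plan still to be written. With one scheduled swab after baseline there are no two complete datasets to choose between, so the likely outcome is that day 21 is used. That is fair, and it makes deliberate choice of the day after seeing results unlikely. It does not remove the contradiction: an analysis plan could pick one day, but it would still conflict with one section of the protocol.

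Three narrower points also stand.

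- Only the 3% contact rate carries a time. The cure rates of 3%, 10% and 30% for infected women carry none, so a mismatch with day 21 is not shown for them. What can be asked is that their time point be stated.
- The protocol gives no expected number of symptom-triggered swabs. Many of the 100 symptomatic women might qualify for one. It is safe to call these swabs selected, but their frequency is unknown.
- Correcting the analysis text is a wording change, but restating the contact rate could alter the required number of women.

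**Conclusion.** The concern holds and must be fixed. Both listed primary comparisons use a day that conflicts with the primary endpoint, and none of the 714 planned women has a scheduled sample for it. This is a misstatement in the protocol, not detail left for the analysis plan.

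The conclusion rests on the protocol text alone and needs no outside assumption. The effect on power for the contacts is unquantified, because the only rate given is the two-week 3%. For the infected groups, the documents show only that the cure rates have no stated time.

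**What to change.** 1. In the section on statistical models and methods of analysis, change day 14 to day 21 in both primary comparisons. This matches the Primary endpoint section, the Synopsis, the visit text and Table 1. State a window around day 21 for accepting the swab; this could sit in the analysis plan. **Cost:** wording only, with no added visit or sample.
2. In the Sample size section, restate the control-arm infection rate for contacts as a day-21 value with its basis, and recalculate the number per arm. Give the time point to which the three cure rates refer. **Cost:** one recalculation, which may move the 257 per arm and hence the recruitment target.

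Keeping day 14 instead would require a new swab visit and a rewritten primary endpoint. Aligning to day 21 is the smaller change.
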